**Methods/design:**

A 24-week cluster randomized, double-blind, placebo-controlled study will be conducted on 104 adults ≥70 years. Nursing homes will be randomized to either of four groups: Ex-HMB (exercise intervention with HMB), Ex-Plac (exercise intervention with placebo), NoEx-HMB (no exercise intervention with HMB), and Controls (No exercise and no HMB). Intervention groups which include exercise will complete the individualized multicomponent (strength, balance and cardiovascular exercises) training program VIVIFRAIL. Intervention groups which include HMB supplementation will receive a 3 g/daily dose of free acid HMB in powder form. The primary outcome measure is the functional capacity. Secondary outcome measures are muscle strength and power, frailty and fall risk, body composition, biochemical analyses and cardiometabolic risk factor, disability and comorbidity, cognitive function and depression.

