### Sample size

The required sample size will be determined on the basis on the functional capacity, using the Short Physical Performance Battery (SPPB) [42]. According to previous research on subjects with similar characteristics [17], a clinically relevant change is about 1.5 ± 1.0 points increments after 12-weeks. Differences of 2 point in total SPBB with a standard deviation of 3 points with a power of 80% and α of 0.05 can be estimated with 20 participants using the R software (v. 3.2.1) and the package *samplesize*. Assuming a maximum loss of follow-up of 30%, we will recruit 26 adults ≥70 years per group (*n* = 104). Similar interventions had an adherence rate of 75%, and a mean attendance of 80% to the sessions [17]. Therefore, the current estimation is realistic and affordable.

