### Statistical analysis

Analysis will be performed on participants who attended at least 80% the training sessions and completed all the measurements. Treatment effects will be tested using generalized linear models. All models will be adjusted for the baseline outcome value and repeated adjusting for gender, age, the group effect, and confounding factors.

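### The allowance for 30% loss multiplies by 1.3 instead of dividing by 0.7, so 26 per group leaves about 18 evaluable, not 20

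*Protocol article*

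**What the plan says.** The Sample size section of the protocol article sets out the calculation in three steps.

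- Target: "Differences of 2 point in total SPBB with a standard deviation of 3 points", "with a power of 80% and α of 0.05".
- Base number: this "can be estimated with 20 participants using the R software (v. 3.2.1) and the package" named there.
- Inflation: "Assuming a maximum loss of follow-up of 30%, we will recruit 26 adults ≥70 years per group", giving 104 over four groups. The abstract repeats the total of 104.

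The words *per group* do not stand beside the 20, but the next sentence raises it to 26 per group, so 20 must be a per-group number. The same section then cites 75% adherence and 80% mean attendance from similar interventions and concludes that the estimate is realistic.

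The Statistical analysis section limits the analysis to "participants who attended at least 80% the training sessions and completed all the measurements". People who are lost therefore do not contribute to the analysis.

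**The concern.** An allowance for loss should ensure that the required number is still there after the loss has happened. The loss is a fraction of those recruited, so the required number has to be divided by the fraction retained. Adding 30% of the required number to itself gives a smaller figure, and the gap widens as the loss rate rises.

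At stake is whether the recruitment target delivers the evaluable number that the plan itself sets. If it does not, the stated 80% power is not protected at the loss rate the plan says it allows for, and readers credit the design with a margin that it lacks. Because the analysis set admits only participants with complete measurements, each loss comes straight off the analysed number.

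**Working it through.** **Inputs** (Sample size section unless noted): base n = 20 per group; maximum loss d = 30%; recruited = 26 per group, 4 groups, 104 in total (also in the abstract); difference 2, SD 3, so standardised effect 2/3; power 80%; α = 0.05. Sidedness is not stated; two-sided is assumed, and one-sided is also tried.

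**1. Reproduce the plan's 26.**
- n × (1 + d) = 20 × 1.3 = 26.0, an exact match.
- n / (1 − d) = 20 / 0.7 = 28.57, rounded up to 29. Rounding cannot turn this into 26.

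**2. What 26 per group delivers at 30% loss.**
- 26 × 0.7 = 18.2 per group, about 18.
- 104 × 0.7 = 72.8, about 73 in total, against 4 × 20 = 80 required.

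**3. What would be needed.**
- 29 per group: 29 × 0.7 = 20.3, enough. 28 per group: 28 × 0.7 = 19.6, not enough.
- 4 × 29 = 116, which is 12 more than 104 (3 per group).

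**4. The loss that 26 does cover.**
- 1 − 20/26 = 23.1%.

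**5. Which test gives a base of 20?** Sample size per group at effect 2/3, 80% power, α = 0.05:

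| t-test | Two-sided | One-sided |
|---|---|---|
| One-sample or paired | 19.67, so 20 | 15.36, so 16 |
| Two-sample | 36.3, so 37 | 28.5, so 29 |

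Only the two-sided one-sample or paired test reproduces 20.

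**6. Power lost through the inflation step** (two-sided t-test, effect 2/3):

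| Evaluable per group | One-sample or paired | Two-sample |
|---|---|---|
| 20 | 80.7% | 53.8% |
| 18 | 76.0% | 49.3% |
| Difference | 4.7 points | 4.5 points (4.4 before rounding) |

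On either test the step costs 4 to 5 points.

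**7. Does the error carry over to another base?** Yes. From 37 per group, × 1.3 gives 48.1, so 49, of whom 49 × 0.7 = 34.3 remain. Dividing gives 37/0.7 = 52.9, so 53, of whom 53 × 0.7 = 37.1 remain.

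**The case against.** **The effect is small, and 30% is a maximum.** This stands as a limit on size. Any loss up to 23% keeps 20. If the cited 75% adherence is read as retention, 26 × 0.75 = 19.5 remain, with power of 79.6% on the test that reproduces 20. But the sentence claims to cover 30%, and at 30% it does not.

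**The exclusions in the analysis set.** A reader might infer that exclusions for low attendance or missing measurements come on top of the 30%. The protocol does not settle this. The label given to the 30% is loss of follow-up, which points to a separate cause. Yet the next sentences cite adherence and attendance before calling the estimate realistic, so the authors may have meant one allowance for everything. People with missing measurements also overlap with those lost, and the attendance rule can bite only in the two exercise groups. What can be said is that the coverage of the 30% is not stated, and that the shortfall is larger if it leaves these exclusions out.

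**A power of 49%.** A reader might take the two-sample figure at 18 per group as the cost of this slip. It is not: the two-sample power is already 53.8% at 20. Most of the gap to 80% comes from the base number, which is a separate matter.

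**A one-sample test.** A reader might conclude that the authors planned one. The protocol names neither the test nor the sidedness. That only this test returns 20 is an inference from the numbers, not something the document says.

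**Conclusion.** The figure is wrong as written. The plan requires 20 evaluable per group, assumes up to 30% loss and recruits 26, which leaves about 18. Meeting its own requirement would take 29 per group (116 in total). Nothing elsewhere in the article repairs this, and base, loss rate and target are all printed, so it is not detail left to a fuller document.

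The size is modest: about 2 evaluable participants per group, and about 5 power points in the worst case that the plan allows for. This rests on reading 20 as a per-group number, on a two-sided α of 0.05, and on the one-sample or paired t-test as the calculation behind the 20. The arithmetic on numbers (18.2, 29, 23.1%) depends only on the first of these. The finding does not show that the trial's power collapses because of the inflation step. Whether 20 is the right base for comparing two groups is a separate and larger question.

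**What to change.** Correct the inflation sentence in the Sample size section in one of two ways:

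- state that 26 per group keeps 20 evaluable for losses up to 23%; or
- state that a 30% loss leaves about 18 per group, and give the power at that number for the comparison actually planned, naming the test and its sidedness.

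In either case, state whether the 30% is meant to include participants whom the Statistical analysis section excludes for attendance below 80% or for any missing measurement. If the base number is recalculated, inflate it with n/(1 − 0.30).

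These are changes of wording and need no change to recruitment or conduct. The cost is a less favourable statement: a margin of 23% instead of 30%, or a power below 80%. With the second option, if the planned comparison is between two groups, the power to be printed is far below 80%, mainly because of the base number. The two issues are therefore best settled together.

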## Methods/design

### Study design and settings

This is a cluster randomized, placebo-controlled study with four parallel groups. The study has been designed to determine the efficacy of HMB supplementation in addition to 24-weeks of multicomponent exercise and resistance training (the VIVIFRAIL program) in adults ≥70 years. Flowchart of the trial is shown in Fig. 1. Enrollment, intervention allocation, follow-up, and data analysis will be conducted according to the SPIRIT (Standard Protocol Items: Recommendations for Interventional Trials) statement [39, 40].

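### The sample size allows for loss to follow-up only, but the analysis also drops residents below 80% attendance, so the two exercise arms are likely to fall short of the 20 per group behind the power claim, by an amount the protocol does not fix

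*Protocol article*

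**What the plan says.** The Sample size section of the protocol article works from "Differences of 2 point in total SPBB with a standard deviation of 3 points with a power of 80% and α of 0.05" and says that this "can be estimated with 20 participants using the R software (v. 3.2.1"). It then sets recruitment: "Assuming a maximum loss of follow-up of 30%, we will recruit 26 adults ≥70 years per group", 104 in all. Loss to follow-up is the only reason given for going from 20 to 26. The section closes with reassurance from an earlier study: "Similar interventions had an adherence rate of 75%, and a mean attendance of 80% to the sessions [17]. Therefore, the current estimation is realistic and" (sentence cut short here).

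The Statistical analysis section defines the only analysis set in the article: "Analysis will be performed on participants who attended at least 80% the training sessions and completed all the measurements".

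Training sessions exist only in Ex-HMB and Ex-Plac (Multicomponent physical exercise program), so the attendance condition can remove residents only from those two arms.

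**The concern.** The two sections do not describe the same number of people. One sizes the trial for residents who stay in follow-up. The other analyses those who stay, have every measurement and also pass an attendance threshold. That threshold sits at the mean attendance the protocol itself expects. Unless attendance is distributed unusually, a sizeable share of retained exercise residents will fall below it. The attendance figure offered as reassurance therefore points to an exclusion that the calculation never counts.

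Ex-HMB against Ex-Plac is the contrast that answers the stated question of HMB added to exercise. If both arms shrink well below the planned number, the stated 80% power does not describe the planned analysis, and a null HMB result could not be taken as evidence of no effect.

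**Working it through.** **Inputs from the protocol (Sample size):** difference 2 points; SD 3; power 80%; alpha 0.05 (taken as two-sided, since the article does not say); 20 evaluable, read as per group because 26 per group follows from it; maximum loss 30%; cited adherence 75% and mean attendance 80%. **From Statistical analysis:** attendance of at least 80% and complete measurements.

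**Not in the documents, so assumed:** the share of retained residents who reach 80% attendance. I take the 30% loss to cover incomplete measurements as well.

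**1. The plan's own figures.**
- A one-sample or paired two-sided t-test with 2 points and SD 3 gives n = 20 (power 80.7%).
- A two-sample t-test with the same inputs needs 37 per group (36 by the normal approximation) and has 53.8% power at 20 per group.
- 20 × 1.3 = 26 reproduces the recruited number. At the full 30% loss, 26 × 0.70 = 18.2 remain before any attendance exclusion.

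**2. Analysable number per exercise arm** = 26 × (1 − loss) × share reaching 80% attendance.

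| Reading | Calculation | Analysable |
|---|---|---|
| 30% loss, share 50% | 26 × 0.70 × 0.50 | 9.1 |
| 30% loss, share 65% | 26 × 0.70 × 0.65 | 11.8 |
| 30% loss, share 75% | 26 × 0.70 × 0.75 | 13.7 |
| 30% loss, share 80% | 26 × 0.70 × 0.80 | 14.6 |
| No loss, share 50-65% | 26 × 0.50 to 26 × 0.65 | 13.0-16.9 |
| 30% loss, every completer passes | 26 × 0.70 | 18.2 |
| 75% adherence covers both losses | 26 × 0.75 | 19.5 |

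One way to motivate the share is a beta distribution with mean 0.80. For SDs of 0.05, 0.10, 0.15, 0.20 and 0.25 it puts 0.525, 0.552, 0.582, 0.616 and 0.655 at or above 0.80. Multiplied by 18.2, these give 9.6, 10.0, 10.6, 11.2 and 11.9. Both the shape and the SDs are assumptions.

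**3. What 20 would require.** 20/26 = 77% of those recruited must be retained, fully measured and at or above the cut-off. With no loss at all and a share of 80%, the count is 26 × 0.80 = 20.8, so 20 is reachable, but only at that favourable end. At the full 30% loss it is out of reach whatever the attendance (18.2 < 20).

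**4. Power for 2 points, SD 3, two-sided 0.05** (equal arms, two-sample t-test, unadjusted, clustering ignored):

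| Per arm | 9 | 12 | 14 | 18 | 19 | 20 |
|---|---|---|---|---|---|---|
| Power | 26.5% | 34.6% | 39.7% | 49.3% | 51.6% | 53.8% |

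**The case against.** The strongest reply is that the size of the shortfall cannot be read from the protocol. A mean of 80% does not fix how many residents lie above 80%. The 30% is a stated maximum, not an expectation. The article does not say whether the cited mean attendance refers to completers or to everyone enrolled. If it is everyone, dropouts are among the low attenders and multiplying the two losses counts them twice. For example, 30% dropouts averaging 45% attendance and 70% completers averaging 95% give 0.30 × 45 + 0.70 × 95 = 80% overall. Every completer could then pass, leaving 18.2. The 75% adherence rate is undefined; if it covers both losses, 26 × 0.75 = 19.5, practically the planned 20, and the reassurance becomes coherent.

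All of this stands. A reader might infer that the plan's own attendance figure implies about 10-12 analysable residents per exercise arm. The documents do not support that: it needs an assumed attendance distribution, the full 30% loss and losses that do not overlap.

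It can also be said that the attendance gap is secondary, because 20 matches only a one-sample or paired test and a two-sample comparison at 20 per arm has about 54% power anyway. That is right, and it means the power must be restated for the between-group comparison whatever is done about attendance. The planned baseline adjustment could also move these power figures, as could clustering. None of this supplies the missing allowance for attendance exclusions.

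**Conclusion.** The point holds as a mismatch between two written rules. The recruitment target allows for loss to follow-up only, while the analysis set also excludes on attendance, at a cut-off equal to the cited mean. The exercise arms are likely to fall short of 20, by an amount the documents do not fix.

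Assuming the full 30% loss and 50-80% of completers reaching the cut-off, about 9-15 per arm are analysable. With less loss, dropouts overlapping with low attenders, or 75% adherence covering both, the figure rises to about 17-19.5. Two-sample power over this span runs from about 27% to 52%, against the stated 80%. These power figures are unadjusted and ignore clustering. It would go too far to say that the arms cannot reach 20, since negligible loss with high attendance would allow it. It would also be wrong to treat 20 as sufficient for a comparison between groups.

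**What to change.** Preferred: remove attendance from the definition of the primary analysis set and keep the 80% rule for a secondary per-protocol analysis. Then restate the power in Sample size for the number expected, 26 × 0.70 = about 18 per arm, which gives about 49% on a two-sample test with the stated inputs. Removing the rule does not by itself restore 20 or the 80% power, so the restatement is needed too.

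Alternatively, if the attendance rule stays in the primary analysis, state the expected analysable number per exercise arm as a range, with the assumed share reaching 80% and the assumed loss, and give the power for that range.

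In either case, delete the sentence calling the estimate realistic, or recalculate it on the number the analysis will contain.

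The cost is a revised sample size paragraph, one recalculation and, for the preferred option, a changed analysis-set definition. The stated power becomes less favourable. Neither option in itself adds participants or procedures.

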### Recruitment process and measurements procedures

A schematic overview of the outcomes, measures and timeline is shown in Table 2. Recruitment will be carried out in nursing homes in Murcia (Spain) located within a radius of 15 km or less than 20 min by car from the assessment sites. There are over 15 nursing homes among this radius that ensure recruitment of enough participants. Initial assessment will be carried out in the Human Performance & Sports Science Lab, Faculty of Sport Sciences, University of Murcia (Murcia, Spain). Body composition and biochemical analyses will be performed in the Medical Centre Virgen de la Caridad (Murcia, Spain). Participants will be scheduled in small groups to be taken to the laboratory for the initial assessment and medical centre. Dependent people will be transported in adapted vehicles with a caregiver. All measurements will be performed under technical and medical supervision.

**Table 2 Tab2:** Schedule of enrollment, interventions, and assessments

TIMEPOINT	Enrollment -t_1_	Allocation 0	Baseline t_1_	Intervention	Follow-up 12th week post baseline t_2_	Close-out 25th week post baseline t_3_
ENROLLMENT						
Eligibility screen	✓					
Informed consent	✓					
Randomized Allocation		✓				
INTERVENTION				✓		
Ex-HMB				✓		
NoEx-HMB				✓		
Ex-Plac				✓		
Control				✓		
ASSESSMENTS						
*Functional capacity (primary outcome)*						
SPPB: Gait speed, balance, and 5-sit-to-stand	✓		✓		✓	✓
*Muscle strength and power*						
Grip strength			✓		✓	✓
1RM seated leg press			✓		✓	✓
1RM vertical bench press			✓		✓	✓
Sit-to-stand muscle power			✓		✓	✓
*Frailty and fall risk*						
Frailty phenotype			✓		✓	✓
Falls history	✓		✓		✓	✓
Fall risk assessment	✓		✓		✓	✓
*Body composition*			✓			✓
*Blood pressure and resting heart rate*			✓		✓	✓
*Haematology*			✓		✓	✓
*Biochemical analyses*			✓		✓	✓
*Nutritional status*			✓		✓	✓
*Sarcopenia*			✓		✓	✓
*Disability and comorbidity*						
Barthel index			✓		✓	✓
Lawton index			✓		✓	✓
Comorbidity			✓		✓	✓
*Cognitive function*	✓		✓		✓	✓
*Depression*			✓		✓	✓

Ex: 12-week of VIVIFRAIL multicomponent exercise program. HMB: dietary supplementation of HMB. *Plac* Placebo. *SPPB* Short Physical Performance Battery; *1RM* one-repetition maximum

The VIVIFRAIL exercise program will be administered by a training team (experienced and qualified personal trainers and physical therapists), under nursing supervision. After the initial assessment and one week before the start of the intervention, participants will attend a familiarization session at the place in which the testing and training will be conducted.

### Randomization and blinding

After recruitment and baseline measurements, nursing home will be randomized to either of the four groups in clusters, according to a computer-generated sequence using the Sealed Envelope Ltd. online system. The cluster design is chosen to prevent influences on participants’ behaviours within a given nursing home unit. A stratified randomization will be used according to their initial functional status (A, B, C or D, see Fig. 2) to reduce imbalance between groups. The allocation will be concealed in a password protected computer file. Given the nature of the treatment (i.e., daily exercise and dietary supplementation program), participants will be aware of their group allocation. Outcome assessors and data analysts will be blinded to the treatment group assignment. Assessors will not be involved in intervention activities. A dedicated protocol will be defined to protect the confidentiality of data.

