#### Multicomponent physical exercise program

Intervention groups including exercise (Ex-HMB and Ex-Plac) will complete an individualized multicomponent training program, VIVIFRAIL [16], 5 days a week during 24 weeks. Free on-line resources and program guidelines are available online (http://www.vivifrail.com/resources). The VIVIFRAIL program has been carefully designed for people ≥70 years and includes six programs or “Passports” adapted for each participant’s condition according to their functional limitation (serious [A], moderate [B], slight [C] and no limitation [D]) and risk of falling (B+ and C+). Individualization is made based on the baseline testing scores (i.e., the VIVIFRAIL test). Each program combines strength, power, balance, walking, stretching and cardiovascular exercises, in the named “VIVIFRAIL Wheel”. Training sessions are daily and weekly organized (type of exercise, steps and reps) in individual “Passports”. A summary of the exercise program is shown in Fig. 2.

The VIVIFRAIL program has a free mobile app available on iOS and Android, the latest version of which, (launched in January, 2019) allows the recording of the results of the test to automatically assign each participant to a training program. The App includes a calendar with a daily progression, training monitoring and rate of perceiving effort assessment.

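### Whole nursing homes are randomised, but the stratification factor is each resident's functional class A–D, so the stratification cannot be applied as written while homes stay intact

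*Protocol article*

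**What the plan says.** Three statements in the protocol article bear on this.

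- **Unit.** Under Randomization and blinding, "nursing home will be randomized to either of the four groups in clusters". The timing is "After recruitment and baseline measurements". The reason given is: "The cluster design is chosen to prevent influences on participants’ behaviours within a given nursing home unit". The title and the abstract also describe a cluster trial, and the abstract names the home as the unit.
- **Stratification.** The same paragraph continues: "A stratified randomization will be used according to their initial functional status". It lists the four classes A to D, points to Fig. 2 for them, and gives the aim as less imbalance between the arms.
- **Meaning of A–D.** Under Multicomponent physical exercise program, the letters label training programmes chosen for each person. The source is that person's own test: "Individualization is made based on the baseline testing scores (i.e., the VIVIFRAIL test".

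The article gives no rule that turns residents' classes into a class for the home, such as a mean, a most frequent class or a share.

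**The concern.** The unit that receives an arm (the home) and the factor said to define the strata (a resident's class) sit at different levels. Whoever runs the allocation has to depart from one of the two statements. If homes are kept whole, the A–D strata have nothing to act on. If a stratified list of residents is used, people in one home go to different arms, which the clustering was meant to avoid.

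Functional class is closely tied to the primary outcome: under Outcome measures, the SPPB scores feed the test that sets the class. With few homes per arm, chance differences in residents' function between arms are likely to be appreciable. The stratification is the only design-stage protection against them that the article describes. Once homes have been allocated, the allocation cannot be repaired.

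**Working it through.** The article states no figure for this point, so there is none to reproduce. The check is whether the rule can be executed, followed by a count of cells.

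**Inputs from the article:** 4 arms; 4 classes; 104 participants (Sample size); more than 15 homes within the recruitment radius (Recruitment process and measurements procedures). **Assumed:** the number of homes randomised, taken as 8 to 16; the distribution of classes; independence of residents' classes within a home.

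**Step 1: does a home belong to one stratum?** Only if all its enrolled residents share one class. For *m* residents and class proportions *p*₁ to *p*₄, the probability is Σ *p*ᵢ^*m*. With 15 homes, 104/15 = 6.9, so take *m* = 7. With 8 homes, *m* = 104/8 = 13.

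| Assumed class mix | m = 7 | m = 13 |
|---|---|---|
| Four equal classes, 4 × 0.25^m | 0.02% | below 0.0001% |
| One class 70%, others 10% each, 0.7^m + 3 × 0.1^m | 8% | 1% |
| One class 90%, others 3.3% each, 0.9^m + 3 × 0.033^m | 48% | 25% |

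Even when nine residents in ten share a class, more than half of homes would be mixed. Homes that specialise in one level of dependency would break the independence assumption and raise these figures. The article does not suggest that homes were chosen that way.

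**Step 2: suppose each home could be given a class.** The cells number 4 strata × 4 arms = 16.

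| Homes randomised (assumed) | Homes per arm | Homes per cell | Residents per home |
|---|---|---|---|
| 8 | 8/4 = 2 | 8/16 = 0.5 | 104/8 = 13 |
| 12 | 12/4 = 3 | 12/16 = 0.75 | 104/12 = 8.7 |
| 16 | 16/4 = 4 | 16/16 = 1.0 | 104/16 = 6.5 |

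A stratum balances the four arms only when it holds a multiple of four homes. At 16 homes every stratum would need exactly four, or some other split into multiples of four. At 8 homes at least two strata would have to be empty. A home-level version of A–D would therefore still give little balance.

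**Step 3: is a usable home-level measure available before allocation?** The text puts allocation after baseline, whereas Table 2 shows the allocation column before the baseline column. The two should be reconciled. Table 2 also marks SPPB at enrolment, so a mean SPPB per home exists before allocation under either order.

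**The case against.** The best defence is that this is a condensed article and that homes can be stratified on a summary of residents' classes. The pronoun in the stratification sentence could refer to the homes, and the figure it cites is not shown. That a home-level rule could be written is true, so stratifying homes by function is not impossible in principle. But the only definition of A–D in the text is individual, and the caption of that figure also speaks of individualisation from baseline scores. The article states two rules at incompatible levels, which goes beyond leaving out a detail. Step 2 also shows that four home-level classes would be too many.

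The second defence is that Statistical analysis adjusts every model for the baseline value of the outcome. This stands in part. Because SPPB feeds the class, adjusting for baseline SPPB deals with much of the imbalance that the strata were aimed at. It does not tell anyone how to allocate homes, and it does not restore precision lost to imbalance.

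A reader might also infer that homes will be split between arms, or that the unit of allocation is open. The documents do not support this: the title, abstract and Methods all describe a cluster trial, and nowhere are individuals allocated. Nor does the article promise balance; it says only that imbalance is to be reduced.

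**Conclusion.** The point holds in this form: stratification by A–D, as defined, cannot be carried out on intact homes, and carrying it out on residents would contradict the reason for clustering. This follows from the text alone. The size of the problem rests on assumptions. At about 7 enrolled residents per home, between 52% and nearly 100% of homes would be mixed under the class distributions tried. With 8 to 16 homes randomised there would be 0.5 to 1 home per cell even with a home-level class.

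The likely consequence is that the stated protection against imbalance in function does little or nothing. Baseline adjustment softens the effect on the SPPB comparison. It should be settled before homes are allocated.

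A reader might go further and conclude that HMB and placebo ought to be randomised within homes, which would make stratification by resident possible. The documents do not make that necessary or clearly better. Randomization and blinding says participants will know their allocation and names the supplement among the reasons, so mixing supplements within a home could bring back the influences that clustering is meant to prevent.

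**What to change.** Replace the A–D stratification with covariate-constrained randomisation of homes, or with minimisation if homes enter one after another. Balance on a home-level summary known before allocation, plus home size. Mean enrolment SPPB is the safest summary because it is available under either order of baseline and allocation; the share of residents in class A or B would serve if classes are assigned by then. State the chosen summary, the balance criterion and the number of homes.

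Constrained allocation leaves room for chance even with few homes. With 8 homes, two per arm, there are 8!/(2!)⁴ = 40,320/16 = 2,520 allocations from which to draw an acceptable one. The criterion should be loose enough to leave many of them eligible.

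Keep the adjustment for individual baseline SPPB in the model, or add individual class. Make Table 2 and the text agree on whether allocation comes before or after baseline.

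The cost is a rewritten paragraph, a short allocation program if the named online system cannot do this, and no extra participants or measurements. With constrained randomisation, the homes must be identified and their enrolment SPPB collected before the draw, which the text already plans.
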